##### Secondary outcomes

For all secondary outcomes, except care use and health care costs, between-group differences will be assessed at both 18 and 52 weeks after start of treatment, or earlier if a preliminary endpoint is reached. Between-group differences in time to MCID-based improvement on disability are analysed by plotting Kaplan-Meier curves and comparing them using the log-rank test. Between-group difference in the number of patients with MCID-based improvement on disability (I-RODS and/or INCAT-DS) will be analysed using the chi-square test. Differences between mean change scores from baseline to follow-up with regard to disability, grip strength, muscle strength, sensory impairment, fatigue and pain will be analysed using the two-group *t* test. HRQL follow-up data (derived from the EQ-5D-5L profiles) will be assessed by repeated measurement analysis, using a linear mixed model. Additionally, the 18- and 52-week follow-up scores of these continuous outcome parameters will be analysed using multivariable linear regression models with the follow-up scores as the dependent variables, and treatment groups, the baseline values and the stratification variables as the independent variables. The repeated data structure of the secondary outcomes (data of the complete 52-week follow-up) will also be analysed using linear mixed models with treatment group membership as a fixed-effect and an appropriate random-effect structure.

##### Safety evaluation

AEs reported or assessed during study visits in the first 24 weeks (or within 6 weeks in case of a preliminary endpoint) and AEs identified on patients’ questionnaires (week 18) will be summed up and plotted separately from adverse events reported on the physicians’ questionnaires (week 52). Frequency of (S) AEs, counted once per patient, as well as description, duration, severity score, consequences for IMP administration and outcome is summarised using descriptive statistics. Frequencies will be reported as counts (percentages), per treatment group. AEs are specified by description. Frequencies of patients reporting mild and moderate AEs (combined) and severe AEs are reported. For the physician completed week 52 AE questionnaire, frequencies of patients reporting AEs and specific AEs are reported. Frequencies will be compared between the treatment groups using the chi-square test. In case of low observed counts (< 10) or expected counts (< 5), we will use the Fischer exact test instead of the chi-square test. Frequency of SAEs along with description is reported. Frequency of patients with (S) AEs leading to change in or discontinuation of treatment protocol will be reported.

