### Statistical methods

#### Statistical methods for primary and secondary outcomes {20a}

Baseline assessments, outcome and safety parameters will be summarised using simple descriptive statistics. Continuous, normally distributed variables will be expressed as means and standard deviations; continuous, non-normally distributed and ordinal variables as medians (25th–75th percentiles); and categorical variables as counts and percentages. Normality of data will be explored by a Normal Q-Q Plot and tested by the Shapiro-Wilk test. Statistical uncertainties will be quantified with two-sided 95% confidence intervals. All analyses will be based on the intention-to-treat principle, whereas the primary outcome (the number of patients in remission) and three secondary outcomes (time to improvement on disability, number of patients with improvement on disability ≥ MCID, and number of (S)AEs) will be additionally analysed on per-protocol basis. A two-sided *p* value < 0.05 will be considered statistically significant. We will not correct for multiple testing. Data analyses will be performed blinded for the allocated study intervention.

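### The adverse-event outcome is named as a number of events, but the only between-group comparison counts each patient once, which costs much power if events are common

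*Protocol article*

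**What the plan says.** Objectives {7} lists more or fewer adverse events as a secondary question, and Secondary outcomes under Outcomes {12} names the number of (S)AEs. Statistical methods {20a} repeats this when it lists outcomes for a further analysis: "number of patients with improvement on disability ≥ MCID, and number of (S)AEs) will be additionally analysed on per-protocol basis". In that list one item is a number of patients and the next is a number of events.

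The Safety evaluation section fixes the AE analysis:

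- Unit: "Frequency of (S) AEs, counted once per patient, as well as description, duration, severity score, consequences for IMP administration and outcome is summarised".
- Summary: "Frequencies will be reported as counts (percentages), per treatment group".
- Test: "Frequencies will be compared between the treatment groups using the chi-square test".
- Small counts: "In case of low observed counts (< 10) or expected counts (< 5), we will use the Fischer exact test instead of the chi-square test".
- Breakdowns: "AEs are specified by description", and "Frequencies of patients reporting mild and moderate AEs (combined) and severe AEs are reported".

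The same section sums and plots AEs from visits and from the week-18 patient questionnaire. It also reports SAEs with a description, and patients whose (S)AEs changed or ended the treatment protocol. It names no rate, ratio or test for the event total.

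**The concern.** A count of events and a count of patients with at least one event are different variables. In the overall row, a patient with one mild event and a patient with several events across seven courses contribute the same. If most patients in both arms have at least one AE, that row can barely move, however many extra events methylprednisolone causes.

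What is at stake is a secondary objective. The abstract says the added short- and long-term risks of the combination need to be assessed, and Sample size {14} justifies its large target difference partly by the AEs that methylprednisolone may cause.

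**Working it through.** **The plan's own figure.** The article gives no AE rate and no power for safety, only the sample size for remission. With 0.35 v 0.65, two-sided 0.05 and 80% power: n = [1.96·√(2·0.5·0.5) + 0.842·√(0.35·0.65 + 0.65·0.35)]² / 0.30² = (1.386 + 0.568)² / 0.09 = 42.4, so 43 per group. Then 43/0.90 = 47.8, so 48. Both reproduce, and 48 per arm is used below.

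**Is a high any-AE share plausible?** An AE is any undesirable experience over 24 weeks, related or not (Adverse event reporting {22}). AEs are asked for at baseline, at weeks 6, 12, 18 and 24 (Table 1) and by phone at week 3 (Table 2). Everyone is scheduled for seven IVIg courses, and week 18 adds a structured list of common corticosteroid and IVIg effects. A high share is plausible, but this is inference.

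**Assumptions (not in the article).** AE counts per patient are negative binomial with mean μ and dispersion α from 0.3 to 0.8, with 50% more AEs on methylprednisolone.

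**Step 1: share with at least one AE.** P = 1 − (1 + αμ)^(−1/α). For 4 v 6:

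- α = 0.8: 1 − 4.2^(−1.25) = 0.834 v 1 − 5.8^(−1.25) = 0.889. AE-free patients expected: 8.0 v 5.3 of 48.
- α = 0.3: 1 − 2.2^(−3.33) = 0.928 v 1 − 2.8^(−3.33) = 0.968. AE-free patients expected: 3.5 v 1.5 of 48.

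With so few AE-free patients, the small-count rule sends the table to Fisher's test.

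**Step 2: power of the planned comparison.** Exact binomial enumeration at 48 per arm, using chi-square, or Fisher if any observed cell is below 10 or any expected cell below 5.

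**Step 3: power on counts.** Wald test of the log ratio of mean counts, simulated 20,000 times. Hand check: SE² = (1/μ₁ + α + 1/μ₂ + α)/48. For 4 v 6 and α = 0.8, SE² = 2.017/48 = 0.0420, SE = 0.205, z = 0.405/0.205 = 1.98, power about 51%. For α = 0.3, SE² = 1.017/48 = 0.0212, SE = 0.146, z = 2.79, power about 80%.

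| Assumed means | Any-AE share | Power, planned rule | Power, counts |
|---|---|---|---|
| 0.3 v 0.45 | 24–25% v 32–34% | 12–16% | 18–20% |
| 1 v 1.5 | 52–58% v 63–71% | 18–25% | 35–47% |
| 2 v 3 | 70–79% v 78–88% | 13–15% | 45–65% |
| 4 v 6 | 83–93% v 89–97% | 3–7% | 52–80% |

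Ranges run over the dispersion; simulated values can move by about a point. With no true difference at mean 4, the count test rejects in 5–6% of trials, so its power is slightly flattered, though far too little to explain the gap.

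**Where the loss is small.** For a doubled rate with Poisson counts and a control mean of 0.3, the any-AE share is 26% v 45% and power is 50% on patients against 59% on counts.

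**Comparisons that do not saturate.** Under the same rule at 48 per arm, power is 48% for 5% v 20%, 61% for 10% v 30% and 88% for 20% v 50%. Here sample size is the main limit, and counting events would not fully cure that.

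**The case against.** Counting patients with events is a conventional safety display, and the trial was sized for remission, not harm. The phrase about counting once can also mean once per AE type. On that reading a patient with five kinds of AE appears in five rows, and only the overall row collapses. The section goes beyond one overall proportion: severe AEs, SAEs and treatment-changing AEs are separate and need not saturate, and {20a} promises 95% confidence intervals. A total count gives a mild headache the weight of a severe event and includes IVIg effects common to both arms. The week-18 questionnaire is a one-time list, not an event count. The choice of count model could be left to an analysis plan.

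Most of this stands, and it limits the point. It does not remove the mismatch: the article itself names a number of events, and its section on the AE analysis compares patients. On the per-type reading, recurrences across seven courses are still dropped and the text still needs clarifying.

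A reader might infer that the comparison is certain to saturate, or that it cannot show any difference. The article gives no AE rate, so this does not follow; at low rates the loss is modest. A reader might also infer that a non-significant any-AE test will be reported as no added harm. Nothing in the article says so.

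**Conclusion.** The point holds in a limited form and should be corrected. The outcome is worded as a number of (S)AEs, and the Safety evaluation section fixes no between-group comparison or effect estimate for that number. If AEs are common, the overall any-AE comparison loses most of its power to show a 50% excess: about 3–7% against 52–80% at assumed means of 4 v 6, and 13–15% against 45–65% at 2 v 3. At 1 v 1.5 the gap narrows to 18–25% against 35–47%, and it is small when AEs are rare. These sizes rest on assumed means, on negative binomial counts with dispersion 0.3–0.8, and on reading the overall row as any AE per patient. The non-saturating displays remain informative about severity and type, but none of them estimates the number of events.

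**What to change.** In Safety evaluation:

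1. Keep the once-per-patient frequencies, and state whether they are per patient or per AE type.
2. Add an analysis of the named outcome: AEs per patient recorded on the AE template in the AE recording period, as a rate ratio with 95% confidence interval. Use an overdispersion-robust count model (for example negative binomial) with log observation time as offset, since recording ends sooner after an early endpoint, and with country and previous treatment as covariates.
3. Analyse the week-18 questionnaire items separately, or merge them with visit reports only after removing duplicates.
4. State that a non-significant any-AE test is not evidence of no excess harm.

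The cost is one extra model and, if sources are merged, the work of matching events; the template already collects AEs individually. The drawback is that a total weights mild and severe events equally, so it should be shown beside the severity split.

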##### Long-term efficacy and safety evaluation

Proportion of patients in remission, number of patients with improvement on disability equal or more than the MCID, mean change in disability and physician-reported AEs at week 104 will be analysed as described for the primary and secondary outcomes at 52 weeks. The results of the 104-week assessment will be reported separately.

#### Economic evaluation

##### General considerations

We hypothesise that a combined individualised treatment (IVIg and intravenous methylprednisolone) in CIDP patients leads to more frequent long-term remission compared to treatment with IVIg and placebo. To assess the benefits and harms of the combined individualised treatment, a prospective economic evaluation will be executed alongside the proposed randomised controlled trial. The time horizon is restricted to the initial 1-year follow-up. In addition, an analysis will be performed to extrapolate results reflecting a time horizon of 4 years, including scenarios with altered remission rates. Incremental cost-effectiveness ratios are calculated, reflecting the extra costs per additional patient in remission and the incremental costs per additional quality adjusted life year (QALY) gained. Sensitivity analyses will be performed to account for sampling variability and for differences in unit costs (95% CI, after bias corrected and accelerated non-parametric bootstrapping) [27]. Cost-effectiveness acceptability curves will be drawn to show the probability of cost-effectiveness of the individualised treatment (IVIg and corticosteroids) at various levels of willingness-to-pay per QALY up to 80,000 Euros.

##### Primary objective of the economic evaluation

The economic evaluation will be performed from a societal perspective as an incremental cost-effectiveness analysis (CEA) and an incremental cost-utility analysis (CUA) expressing the benefits of the combined treatment in terms of effectiveness (remission) and QALY’s gained. This will include an assessment of the economic impact of the implementation of the combined treatment (IVIg and corticosteroids) as replacement for IVIg treatment alone.

##### Cost-analysis

The economic evaluation includes health care costs, out-of-pocket expenses, and costs of production loss. Cost data include direct medical (e.g. drug costs (dose, frequency) of IVIg, IVMP, co-medication and co-prescription of other medication, outpatient and in-patient service costs, including (IVIg infusion related) home care), direct non-medical and indirect costs. Direct medical costs are defined as the volumes of health care resource utilisation multiplied by unit prices. Out-of-pocket expenses concerning health-related travel, informal home care, over-the-counter medication and mobility aids will be recorded. Differences in costs will be reported along with 95% CI after bias corrected and accelerated non-parametric bootstrapping [27]. All registered volumes within the participating centres will be valued according to the Dutch costing guideline for health care research [28]. Unit costs of IVIg and corticosteroids will be derived concordant with the Dutch Pharmacotherapeutic Compass and the website www.medicijnkosten.nl of the National Health Care Institute. The friction costs method will be applied to derive the costs of lost productivity, irrespective of age and sex [26, 28]. Costs will be expressed for the base year 2019 and discounting of costs (4%) and effects will be performed. Unit costs from different calendar years will be indexed with general yearly consumer price indices. Transferability of resource utilisation between the Netherlands and the UK will be weighed considering possible case-mix variations. Cost-calculations will be based on clinical pathway components related to the intervention and relapse and actual resource use for both treatments during the study period (e.g. use of IVIg and corticosteroids, in-patient visits, outpatient visits and hospital stay). Data on resources used are directly collected from the hospital information systems, clinical report forms and self-administered health and labour questionnaires (HLQ): *i*MCQ and the *i*PCQ adapted to the study population [26]. Tailoring of these questionnaires included extending the recall to cover the period until the previous completion of the questionnaire, or previous visit in case of a preliminary endpoint.

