### Provisions for post-trial care {30}

After study completion, patients will continue to receive standard care for CIDP. Patient who are stable will not require additional treatment. Patients who reach a preliminary endpoint, defined as deterioration during the 18-week treatment period requiring additional CIDP treatment, no improvement at week 18, restart CIDP treatment for any reason (i.e. a relapse) between week 18–52 or drop out during study for whatever reason will be treated at physician’s discretion and will complete follow-up visits according to protocol. AMC Medical Research BV (AMR) has an insurance which is in accordance with the legal requirements in the Netherlands (Article 7 of the Medical Research Involving Human Subjects Act (WMO) and the Measure regarding Compulsory Insurance for Clinical Research in Humans of 23 June 2003). This insurance provides cover for damage to research patients through injury or death caused by the study for patients in the Netherlands. Where harm to participants arises from the conduct of the research, National Health Services (NHS) indemnity applies. Where harm to participants comes from the design or management of the research, this comes under Sponsor insurance. These arrangements are covered in a coordinator agreement and in the site agreements.

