#### Outcome measures

For disability, we will use the I-RODS and the INCAT-DS. The I-RODS is a patient self-report linearly weighted scale that measures activity and social participation limitations [12, 15]. The I-RODS consists of 24 questions and allows for three response options: (0) impossible to perform, (1) performed with difficulty and (2) easily performed. Scores range from ‘0’ (all activities impossible to perform) to ‘48’ (all activities easily performed). These scores are transformed and expressed in log-odds (logits), ranging from − 6.95 to 8.11. The I-RODS has been developed specifically for inflammatory neuropathies including CIDP and has been validated in a large group of patients [16]. In addition, disability will be measured using the adjusted INCAT-DS, which has been used in numerous CIDP trials [5, 13, 17]. The adjusted INCAT-DS is a 10-point ordinal scale measuring limb disability, ranging from ‘0’ (no arm or leg disability) to ‘10’ (no arm movement possible, wheelchair bound). The reason to choose both disability scales to assess improvement and remission is outlined in the discussion. We will use a handheld Vigorimeter to measure grip strength in kPa, the Medical Research Council (MRC) sum score of 12 predefined muscle groups (including shoulder abduction, elbow flexion, wrist extension, hip flexion, knee extension and foot dorsiflexion) to measure muscle strength, the INCAT- sensory sum score (INCAT-SS) to assess sensory impairment, the Rasch-built Fatigue Severity Scale (R-FSS), the Pain intensity numeric rating scale (PI-NRS) and the EuroQol (EQ-5D-5L) to measure HRQL [18–24]. Health care resources will be measured using working documents and the iMTA Medical Consumption Questionnaire (*i*MCQ) and the Productivity Cost Questionnaire (*i*PCQ), both adapted to the study population [25, 26]. Working documents keep track of IVIg use, outpatient hospital consultations, hospitalizations, and major diagnostic examinations and therapeutic interventions. Tailored *i*MCQ will be used to measure volume of out-of-hospital consultations (general physician, physical therapist, psychologist, etc.), other institutionalizations (temporary rehabilitation, nursing home), day-care treatment, emergency admissions and out-of-pocket expenses by patients. The impact of CIDP on the ability of a person to perform work, production loss following absence from work or personal inefficiencies will be measured with the *i*PCQ. AEs reported spontaneously at visits or otherwise reported by patient or observed by physician, during the first 24 weeks of the study, or in the case of an early endpoint during treatment protocol within 6 weeks of last treatment course, are recorded using an AE template provided by the Amsterdam UMC, Clinical Research Unit (CRU). The AE template consist of a description, severity score (mild, moderate, severe), potential relation to IMP (unlikely, unlikely, possible, probable, definite, not possible to assess), consequences for IMP administration (options including temporary or permanent stops, dose changes), any other actions taken (i.e. start of co-medication, a referral) and the outcome (i.e. resolved). Severity scores will be defined as followed: mild (i.e. an AE that is transient and may require only minimal treatment or therapeutic intervention; the event does not generally interfere with usual activities of daily living), moderate (i.e. alleviated with specific therapeutic intervention; the event interferes with usual activities of daily living, causing discomfort but poses no significant or permanent risk of harm to the research patient) or severe (i.e. an AE that interrupts usual activities of daily living, or significantly affects clinical status, or may require intensive therapeutic intervention). Patients will complete a structured questionnaire with most frequent corticosteroid and IVIg-related AEs at the 18-week visit. These AEs are subsequently scored by the investigator using the previously described severity score. (S)AEs are further described under the ‘Adverse event reporting and harms {22}’ section. Long-term corticosteroid related AEs are also assessed by the investigator at weeks 52 and 104. AE questionnaires are completed after all other outcome assessments have been performed. Patients are asked to indicate which treatment they think they have received, at the end of the study. Outcome measures and assessment visits are listed under the ‘Plans for assessment and collection of outcomes {18a}’ section and shown in Table 1.

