
**Table 1 Tab1:** Study visits and measurements

	Study visits							
	Intervention period (in weeks)				Follow-up period (in weeks)		Safety follow-up (in weeks)	Unscheduled visits (in weeks)
Measurements	BL	6	12	18	24	52	104	0–52
**Blood pressure**	X	X	X	X	X	X		X*
**Body weight**	X			X		X		X*
**HbA1C**	X				X	X		
**AEs**	X	X	X	X	X			X^‡^
**AE questionnaire**^**§**^				X		X	X	X^*¥^
**I-RODS**	X	X	X	X	X	X	X	X
**INCAT-DS**	X	X	X	X	X	X	X	X
**Grip strength**	X	X	X	X	X	X		X
**MRC sum score**	X	X	X	X	X	X		X
**INCAT-SS**	X	X		X		X		X*
**EuroQol**	X	X		X		X		X*
***i*****MCQ**		X		X		X		X*
***i*****PCQ**		X		X		X		X*
**R-FSS**	X	X		X		X		X*
**PI-NRS**	X	X		X		X		X*

*Abbreviations: BL* baseline, *AE* adverse event, *I-RODS* inflammatory Rasch Disability Scale, *MRC* Medical Research Council, *INCAT-DS* Inflammatory Neuropathy Cause and Treatment Disability Scale, *INCAT-SS* Inflammatory Neuropathy Cause and Treatment sensory sum score, *iMCQ* iMTA Medical Consumption Questionnaire, *iPCQ* iMTA Productivity Cost Questionnaire, *R-FSS* Rasch-built Fatigue Severity Scale, *PI-NRS* pain intensity numeric rating scale. *If the unscheduled visit is considered as a preliminary endpoint visit. ^**§**^This row includes the investigator assessed (long-term) AEs investigated at weeks 52 and 104. ^‡^If unscheduled visits takes place during treatment protocol, within 6 weeks of ending treatment protocol. ^¥^In case of a preliminary endpoint during intervention period, week 18 AE questionnaire is completed by patient and physician

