### Sample size {14}

There are no robust figures on the long-term remission rates in patients treated with IVIg only. In a previous trial, remission during a 6-month period was seen in about half of IVIg responders, compared to 100% in IVMP responders [9]. However, a significant proportion of patients were not treatment naïve but known responders to IVIg. Furthermore, follow-up was shorter than the follow-up period in this study. We assume that the remission rate after IVIg is approximately 35% during an 8-month follow-up period. Treatment-naïve CIDP patients treated with dexamethasone had a long-term remission rate of 56% using a more stringent definition of improvement compared to this study [5, 8]. Our limited prospective pilot data of the OPTIC protocol suggest similar remission rates (59%) [10]. We assume remission rates of 35% in the IVIg/placebo group, and 65% in the IVIg/IVMP. A 30% difference in remission rate is large but warranted as IVMP may lead to various AEs in patients and because there is the alternative of continuing maintenance IVIg treatment. A two-group chi-square test with a 0.05 two-sided significance level will have 80% power to detect the difference between a control group proportion (IVIg/placebo) of 0.35 and a treatment group proportion (IVIg/IVMP) of 0.65 (odds ratio of 3.45) when the sample size in each group is 43 (86 patients in total). Anticipating on a 10% attrition rate due to AEs, we will include 48 (43/0.90) patients in each group (96 patients in total).

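### Read literally, the recall rule for the cost questionnaires leaves six or more weeks uncovered before some preliminary endpoints, in questionnaire-based costs only

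*Protocol article*

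**What the plan says.** The Cost-analysis section of the economic evaluation says that the questionnaires were tailored by "extending the recall to cover the period until the previous completion of the questionnaire, or previous visit in case of a preliminary endpoint". The normal rule is therefore recall to the last completed form, with a different starting point, the last visit, at a preliminary endpoint.

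Table 1 places iMCQ and iPCQ at weeks 6, 18 and 52. The cells for weeks 12 and 24 are empty, although both are study visits. An unscheduled visit carries the forms only under a footnoted condition: "If the unscheduled visit is considered as a preliminary endpoint visit". Participant timeline {13} allows ad hoc visits when a relapse is suspected, so an unscheduled visit need not be an endpoint.

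Provisions for post-trial care {30} gives the preliminary endpoint a wide meaning: "defined as deterioration during the 18-week treatment period requiring additional CIDP treatment, no improvement at week 18", and also "restart CIDP treatment for any reason (i.e. a relapse) between week 18–52 or drop out during study for whatever reason". These patients continue with the scheduled follow-up visits.

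On sources of cost data, Outcome measures states: "Working documents keep track of IVIg use, outpatient hospital consultations, hospitalizations, and major diagnostic examinations and therapeutic interventions". For the questionnaires it states: "Tailored *i*MCQ will be used to measure volume of out-of-hospital consultations", together with other institutional stays, day care, emergency admissions and out-of-pocket expenses; and "production loss following absence from work or personal inefficiencies will be measured with the *i*PCQ".

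**The concern.** At weeks 12 and 24, and at unscheduled visits that are not endpoints, the last visit and the last completed form are different dates. Starting recall at the last visit then skips the weeks between the two. The next scheduled form does not recover them, because it reaches back only to the form completed at the endpoint.

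The skipped weeks arise only in patients who reach a preliminary endpoint, so coverage of resource use depends on outcome. If endpoints are more frequent in one arm, that arm's questionnaire-based costs are undercounted more. Reduced healthcare costs are a stated secondary objective, and the evaluation takes a societal perspective that includes out-of-pocket expenses and lost production, which come from these forms.

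The gap would also be hard to see. The rule under Missing HLQ data concerns values missing within a questionnaire. A fully completed form with too short a recall period has no missing value to flag.

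**Working it through.** The plan gives no figure for recall coverage. Its sample size reproduces (43 per group for 35% versus 65%, 48 after 10% attrition), but only the remission rates are used below.

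**Step 1: the gap by endpoint time.** Inputs from Table 1: visits at weeks 6, 12, 18, 24 and 52; cost forms at weeks 6, 18 and 52. The week-3 contact is a telephone consultation and is not counted as a visit.

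Gap = (last visit before the endpoint) − (last completed cost form before the endpoint).

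- Endpoint after week 6, up to week 12: 6 − 6 = 0 weeks
- Endpoint after week 12, up to week 18: 12 − 6 = 6 weeks (weeks 6–12)
- Endpoint after week 18, up to week 24: 18 − 18 = 0 weeks
- Endpoint after week 24: 24 − 18 = 6 weeks (weeks 18–24)

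Six weeks is 6/52 = 11.5% of the one-year horizon. Including week 18 itself in the second window assumes that the short recall also applies when the endpoint is lack of improvement at that scheduled visit. A non-improver would then recall to week 12 and an improver to week 6, on the same form at the same visit.

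**Step 2: unscheduled visits.** A non-endpoint visit at week 40 followed by an endpoint at week 42 gives 40 − 18 = 22 weeks uncovered.

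**Step 3: share of relapses affected.** If relapses were uniform over weeks 18–52 (assumption), (52 − 24)/(52 − 18) = 28/34 = 82% would fall after week 24. The mean loss per relapse would be 0.82 × 6 = 4.9 weeks.

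**Step 4: loss per randomised patient, before unscheduled visits.** Sample size {14} states: "We assume remission rates of 35% in the IVIg/placebo group, and 65% in the IVIg/IVMP". Failure is then 65% and 35%. Let q be the share of failures whose endpoint falls in a gap window, assumed equal in both arms. The documents give no value, so take 25% to 100%. Loss = 6 × failure rate × q.

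- Placebo: 6 × 0.65 × 0.25 = 0.98 to 6 × 0.65 × 1 = 3.9 weeks
- IVMP: 6 × 0.35 × 0.25 = 0.53 to 6 × 0.35 × 1 = 2.1 weeks
- Difference: 6 × 0.30 × q = 0.45 to 1.8 weeks, or 0.9% to 3.5% of 52 weeks

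This treats every failure as a preliminary endpoint, which overstates the loss. The fourth failure criterion under Primary outcome, improvement not sustained at week 52, is not in the list of preliminary endpoints. A patient who fails only on that criterion completes the ordinary week-52 form with recall to week 18 and loses nothing.

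**Step 5: dependence on the assumed effect.** Placebo's share of the lost weeks, with equal q:

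- 35% versus 65% remission: 0.65/(0.65 + 0.35) = 65%
- 35% versus 50%: 0.65/(0.65 + 0.50) = 57%
- no difference: 50%

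**The case against.** The strongest reply is that the clause is loosely worded. The evident purpose of extending recall is continuous coverage. The clause could mean that the form after an endpoint looks back to the endpoint visit, and then there is no gap. The article condenses a full protocol, and the tailored questionnaires are not shown, so the forms themselves may carry the right instruction.

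This reading is possible but weak. Table 1 has the forms completed at an unscheduled endpoint visit, so recall to the previous completion already gives that result and the extra clause would add nothing. It changes the recall period only on the reading that creates the gap. What stands is that an actual loss of data cannot be shown from the article, only that the stated rule produces one.

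A reader might also infer that costs in general are lost, mainly on placebo, and that the cost-effectiveness ratios are materially biased against the combination. The documents do not support that:

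- IVIg use, outpatient hospital care, hospitalisations and major procedures come from working documents, with hospital systems and case report forms as further sources. The budget impact analysis centres on IVIg expenditure.
- In the relapse case the uncovered weeks precede the endpoint. Care after relapse is still covered by the later form.
- The placebo excess is an inference from the design rates and from similar endpoint timing.
- Drop-out for any reason is a preliminary endpoint, and the sample-size section anticipates 10% attrition due to adverse events. More such drop-outs on IVMP would work the other way.
- No money value can be attached, and the plan does not say that an uncovered interval is costed at zero.

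**Conclusion.** The point holds as a defect in the stated rule with a modest effect. Read literally, recall at a preliminary endpoint omits weeks 6–12 or weeks 18–24, depending on when the endpoint occurs, and more if a non-endpoint unscheduled visit came first. The omission is limited to out-of-hospital care, other institutional stays, day care, emergency admissions, out-of-pocket expenses and productivity loss, and to patients with a preliminary endpoint.

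Under 35% versus 65% remission and equal endpoint timing, placebo would lose 0.45 to 1.8 weeks more per randomised patient, before unscheduled visits and with every failure counted as an endpoint. The true difference on those assumptions is smaller, because some failures are not preliminary endpoints. It is zero if the arms do not differ, and adverse-event drop-outs could offset it. If it arises as assumed, it understates placebo-arm costs and so works against the combination. The case for correcting it is that coverage depends on outcome and the repair is simple, not that a large bias has been shown.

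**What to change.** In the Cost-analysis section and in the questionnaire instructions, set recall at every administration, including a preliminary endpoint, back to the date of the previous completed iMCQ/iPCQ, or to the start of treatment if none has been completed. Delete the closing clause that switches to the last visit. Printing the start date on each form would make the period plain to the patient.

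If forms have already been collected with the shorter recall, treat the uncovered interval as missing, not as zero use. Trial status reports 34 of 96 patients enrolled, so at that point most forms were still to come.

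The cost is one sentence and a date field. The downside is longer recall at some endpoint visits, but never beyond the 52 − 18 = 34 weeks already accepted for the week-52 form.
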